
#### 2.8.5. Antimicrobial photodynamic therapy.

The Valo Cordless Ultradent® LED curing light will be used. This device has a coupled radiometer, spectrum of 440 to 480 nm and irradiance of 450 mW/cm. Only the volunteer being treated, and operator of the device will be present at the time of aPDT, both of whom will be using protective eyewear. The active LED tip will be covered with disposable transparent plastic wrap (PVC) to avoid cross-contamination and for hygiene purposes and the operator will be duly garmented.

One session of aPDT will be performed with the annatto photosensitizer at a concentration of 20% (Fórmula e Ação®) in spray form to be applied in a sufficient quantity to cover the middle third and dorsum of the tongue (5 sprays) with 2 minutes for incubation. The excess will be removed with an aspirator while maintaining the surface moist with the photosensitizer without the use of water. Six points will be irradiated with a distance of 1 cm between points, considering the light scattering halo and effectiveness of aPDT. The device will be previously calibrated with a wavelength of 395 to 480 nm, 20 seconds per point and energy of 9.6 J. The light will be irradiated such that a halo will be 2 cm in diameter per point. Table 1 displays the parameters that will be used.^[30]^

**Table 1 T1:** LED parameters.

Wavelength (nm)	395–480
Operating mode	Continuous
Mean radiant power (mW)	480
Polarization	Random
Aperture diameter (cm)	0.9
Irradiance at aperture (mW/cm^2^)	762
Beam profile	Top hat
Irradiated area (cm^2^)	3.14
Irradiance at target (mW/cm^2^)	153
Exposure time (s)	20
Radiant exposure (J/cm^2^)	6.37
Radiant energy (J)	9.6
Number of points irradiated	6
Area irradiated (cm^2^)	18.8
Number and frequency of treatment sessions	1
Total radiant energy (J)	57.6

LED = light-emitting diode.

#### 2.8.6. Tongue scraping.

Tongue scraping will be performed by the same operator on all participants using posteroanterior movements of the scraper on the dorsum of the tongue, followed by cleaning of the scraper with gauze. This procedure will be performed 10 times on each patient to standardize the mechanical removal of the tongue coating.

#### 2.8.7. Treatment with probiotics.

Pharmaceuticals (capsules or chewable gum) will be prepared at a compounding pharmacy. The products will contain strains of Lactobacillus salivarius WB21 (6.7 × 108 colony-forming units) and xylitol (280 mg). Each patient should take the pharmaceutical 3 times per day after meals for 7 days.

#### 2.8.8. Brushing with toothpaste containing amine fluoride.

All 52 participants will be instructed to brush with a toothpaste containing amine fluoride (Elmex®) and use dental floss 3 times per day after meals for 10 days.

### 2.9. Statistical analysis

Data from the portable Breath-Alert™ device will be analyzed for normality using the Shapiro–Wilk test. Parametric data will be submitted to analysis of variance followed by Tukey’s test when necessary and the *t* test will be used for paired data to analyze the results of treatment in the 2 periods of the study. Nonparametric data will be compared using the Kruskal–Wallis test followed by the Student–Newman–Keuls test when necessary and the Wilcoxon text will be used for the comparison of each treatment in the 2 periods of the study.

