### 2.6. Calculation of sample size

The sample size will be calculated using data from the study by Costa da Mota et al.^[21]^ An error $err=\left|\underline{x_{1}}-\underline{x_{2}}\right|$ was first established, in which $\underline{x_{1}}$ and $\underline{x_{2}}$ are the means of the groups at baseline for periodontal treatment with PDT. The effect size was calculated based on this error as follows:

$$\begin{array}{l} \frac{err}{\sqrt{\sigma_{1}^{2}+\sigma_{2}^{2}}} \end{array}$$

in which $\sigma_{1}^{2}$ and $\sigma_{2}^{2}$ are the variances of Groups 1 and 2, respectively.

Assuming that the groups studied have normal or approximately normal distribution, that the sample size will be sufficiently large and that a 2-tailed test will be used for a significance level of α = 0.05 and maintaining a test power of 1 − β = 0.90, n = 13 will be needed for each group. Figure 2 shows that a sample of 52 children (4 groups of 13 individuals) would enable demonstrating statistically significant differences while maintaining a test power equal to or higher than 0.90. If the hypothesis of normality of the distributions is rejected, the sample size should be corrected by approximately 5%.

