### 2.7. Randomization

The type of treatment will be determined randomly for each patient prior to the intervention. Randomization will be generated electronically using the randomizer.org site for the balanced distribution of the children among the groups.

Fifty-two mouth-breathing children with a diagnosis of halitosis will be selected and divided into 4 groups.

Group 1: Treatment with brushing, dental floss and tongue scraper;

Group 2: Brushing, dental floss and aPDT applied to the dorsum and middle third of the tongue;

Group 3: Brushing, dental floss and probiotics;

Group 4: Brushing, dental floss, aPDT and probiotics.

Breath meter results will be determined before, immediately after treatment and 7 days after treatment. Microbiological analysis of the tongue coating will performed at the same times. The quantitative analysis will be performed using direct plating and real-time polymerase chain reaction (PCR).

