#### 2.8.2. Breath analysis.

Air from the oral cavity will be collected following the manufacturer’s orientations. The BA will be disinfected after each use. The device will be shaken 4 or 5 times prior to use to eliminate any residual odors. A “beep” is emitted upon opening the upper compartment of the device and a second “beep” is emitted when the volunteer blows into the front air input (passage of airflow). After a third “beep,” the odor of the breath is measured and scored on a scale of 0 to 5 points. An “E” appears when an error has occurred and the procedure is repeated (Fig. 3). A score of ≥2 points is considered indicative of halitosis.

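### Section 2.9 compares the arms without the pre-treatment breath score and lets a normality test on a 0–5 score choose the method; one baseline-adjusted analysis would gain precision at almost no cost

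*Protocol article*

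**What the plan says.** The outcome is the Breath-Alert reading: in section 2.8.2, "the odor of the breath is measured and scored on a scale of 0 to 5 points". Section 2.4.1 admits only children scoring 2 or more, so baseline can take four values. Section 2.7 states that "Breath meter results will be determined before, immediately after treatment and 7 days after treatment". Section 2.6 sets the size: "n = 13 will be needed for each group", 52 in all.

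Section 2.9 first applies Shapiro-Wilk to the breath-meter data. On one branch, "Parametric data will be submitted to analysis of variance", followed by Tukey's test. On the other, groups are compared by Kruskal-Wallis, followed by Student-Newman-Keuls. Separate paired tests (t or Wilcoxon) compare periods within each treatment. No between-group test is given a baseline term, and nothing says that the analysis of variance is run on changes from baseline. Section 2.7 describes balanced allocation but states no stratification by baseline score.

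**The concern.** Section 3 says the trial will show whether the treatments differ, and only the between-arm test answers that. The paired tests use the pre-treatment score, but they describe each arm alone and do not compare treatments. A measurement taken on every child, and likely to be related to the outcome, is therefore left out of the analysis where it would help most. With 13 per arm, chance baseline differences are not small.

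The gate adds a second weakness. An integer score with six levels cannot be normally distributed, so Shapiro-Wilk mainly registers discreteness and sample size. Its result nevertheless decides whether means or ranks are compared and which pairwise procedure follows. That choice matters: Tukey controls familywise error over all pairs, whereas Student-Newman-Keuls with four groups does not when only some of the arms are equal.

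**Working it through.** **The plan's own figure.** Section 2.6 gives two-sided α = 0.05, power 0.90 and 13 per group, but no means, SDs or effect size, so 13 cannot be reproduced. Solved backwards, it needs a standardised difference of √(2/13) × (1.960 + 1.282) = 1.27 (1.33 with the t distribution), or f = 0.54 for the four-group F test.

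**Chance imbalance.** The SD of a baseline difference between two arms is √(2/13) = 0.39 SD. The expected spread from highest to lowest of four arm means is 2.06/√13 = 0.57 SD. A gap above 0.5 SD has probability 0.20 for a given pair and 0.58 (simulated) for at least one of the six pairs.

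**What a gap does.** An unadjusted follow-up contrast moves by r × gap. A 0.5 SD gap moves it by 0.15, 0.25 or 0.35 SD at r = 0.3, 0.5 or 0.7. Conditional on that gap, the type I error of an unadjusted two-arm test at nominal 0.05 is 0.056, 0.065 or 0.067 (normal approximation).

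**Gain from adjustment.** Residual variance is multiplied by 1 − r². The equivalent number of extra children is 52/(1 − r²) − 52. The documents do not give r, so a range is assumed. Power is for the omnibus F test at N = 52 and an illustrative f = 0.40.

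| r (assumed) | 1 − r² | Variance cut | Extra children | Power, unadjusted → adjusted |
|---|---|---|---|---|
| 0 | 1.00 | 0% | 0 | 0.634 → 0.633 |
| 0.3 | 0.91 | 9% | 5 | 0.634 → 0.679 |
| 0.5 | 0.75 | 25% | 17 | 0.634 → 0.770 |
| 0.7 | 0.51 | 49% | 50 | 0.634 → 0.917 |

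**Effect of the entry rule.** Selecting scores of 2 or more narrows baseline and lowers r. This was simulated with a rounded 0–5 score, entry at 2 or more, latent SD 1.2, latent means 2.5 before and 1.8 after, arm shifts of 0, 0.45, 0.45 and 0.9, and 3,000 runs per scenario. All of these settings are assumptions.

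| Latent r | Observed r | Gated rule | ANOVA | ANCOVA | Gain over gated rule |
|---|---|---|---|---|---|
| 0.3 | 0.20 | 0.272 | 0.283 | 0.300 | 2.8 points |
| 0.5 | 0.35 | 0.293 | 0.311 | 0.349 | 5.6 points |
| 0.7 | 0.53 | 0.324 | 0.340 | 0.459 | 13.5 points |
| 0.85 | 0.68 | 0.371 | 0.390 | 0.695 | 32.4 points |

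The Monte Carlo standard error of a power near 0.3 is √(0.3 × 0.7/3000) = 0.008, so the smallest gain is only roughly determined.

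**The gate.** In the same simulations Shapiro-Wilk rejected in 37–54% of single arms of 13, in at least one arm in 85–96% of trials, and in essentially 100% of pooled sets of 52. The branch taken thus depends on whether the test is applied per arm or pooled, which section 2.9 does not state. With no treatment effect, the gated rule rejected in 0.047–0.049 of trials.

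**The case against.** The strongest reply is that covariate adjustment is often left to a statistical analysis plan, which is not shown, and that section 2.9 says only analysis of variance, which could be run on change scores. The first part carries limited weight, because section 2.9 does name its between-group tests, and Kruskal-Wallis as named has no place for a covariate. The second cannot be excluded, but the text does not say so. It would not be the efficient choice either: the variance factor for change scores is 2(1 − r), that is 1.4, 1.0 and 0.6 at r = 0.3, 0.5 and 0.7, against 0.91, 0.75 and 0.51 with adjustment. Below r = 0.5, change scores are less precise than follow-up scores alone.

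Several stronger readings are tempting but unsupported:

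- A reader might infer that the gate makes the omnibus p-value invalid. The simulated type I error stays at its nominal level, and Kruskal-Wallis, where pooled data would almost always lead, is a valid test for an ordinal score.
- A reader might infer that different arms could be analysed by different methods. One omnibus test covers all four arms; only time points, or the within-arm paired tests, could take different branches.
- A reader might infer that chance imbalance biases the result. Randomization keeps the unadjusted comparison unbiased on average. Only part of a gap, in proportion to r, carries over in a given trial.
- A reader might expect the gain at r = 0.7. The documents give no correlation, and truncation at entry makes a lower one plausible.

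**Conclusion.** The point stands as an avoidable loss of precision, not as an invalid analysis. As written, the between-arm tests leave out a baseline score that every child provides, and the choice between them rests on a test that discreteness largely determines. The size depends on the unknown r. A realistic expectation, if the entry rule holds r to about 0.2–0.35, is a gain of about 3–6 power points over the gated rule; it would be considerably larger if r reached 0.5 or more. At r = 0 adjustment costs about 0.1 power point, so the balance favours it across the range. The variance figures assume a linear relation with equal spread across arms, and the power figures rest on the simulation settings listed above. The change should be made before analysis begins.

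**What to change.** Drop Shapiro-Wilk as a decision rule. Prespecify a single between-arm analysis at one named time point (for example day 7): a linear model (ANCOVA) of the breath score on treatment and baseline score, with permutation p-values, reporting between-arm differences with 95% confidence intervals. Fix the pairwise procedure in advance as well. A proportional-odds model with baseline may be added as a sensitivity analysis. It should not be an alternative chosen according to fit, because that would be another data-dependent gate, and 13 per arm over up to six levels risks sparse cells.

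The cost is a change of analysis wording, one degree of freedom, and treating an ordinal score as numeric for estimation. No further children or measurements are needed.

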#### 2.4.1. Inclusion criteria.

Children and adolescents with a diagnosis of mouth breathing determined using a standard questionnaire and halitosis determined using a portable breath meter (score ≥ 2) will be included in the study.

Parents/guardians will provide data on family income, parent’s schooling, child’s previous experience with dental treatment, the occurrence of snoring, open mouth during sleep, daytime sleepiness, saliva on the pillow during sleep, awaking with thirst during the night, dry mouth, nocturnal enuresis, headache, aggressivity, inattention, hyperactivity, abnormal respiration, swallowing difficulty, sense of smell and taste, speaking, negative effect on school performance and the presence of allergies. Parents/guardians will also report their child’s toothbrushing frequency, their participation in brushing, the child’s eating habits, child’s toothpaste, the occurrence of poor oral habits, such as bruxism, nail biting, lip biting, tongue bite, tongue pushing, smacking the lips and whether they have detected bad breath in their child or themselves.

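### Student-Newman-Keuls after Kruskal-Wallis does not guarantee family-wise error control with four groups, whereas Tukey on the parametric branch does

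*Protocol article*

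**What the plan says.** Section 2.9 tests the breath-meter data for normality with Shapiro-Wilk and then takes one of two routes. Data judged normal go to analysis of variance with Tukey's test. Other data go to Kruskal-Wallis, "followed by the Student–Newman–Keuls test when necessary". The section does not say which rank form of SNK is meant, or whether Shapiro-Wilk is run per group, on pooled values or on residuals.

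There are four groups, and section 2.6 states that "n = 13 will be needed for each group". The same section says that "a 2-tailed test will be used for a significance level of α = 0.05"; this level belongs to the sample-size calculation. No family-wise target is stated for the pairwise comparisons.

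In section 2.8.2, "the odor of the breath is measured and scored on a scale of 0 to 5 points". Under section 2.4.1, only children with "halitosis determined using a portable breath meter (score ≥ 2) will be included in the study", so baseline scores are limited to 2 to 5. The Discussion says that the trial will show whether the treatments differ from one another, so the pairwise comparisons carry conclusions.

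**The concern.** SNK orders the groups and tests the widest range first. It then moves inward, using a smaller critical value for each narrower range. Once the wider ranges are rejected, two neighbouring groups are compared at an unadjusted 5%. If all four groups are equal, the first step protects the family. If some groups are equal and others differ, real differences open the outer steps, and more than one true null pair can then be tested at 5%. A significant Kruskal-Wallis test beforehand does not help, because the same real differences make it significant.

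Tukey keeps the four-group critical value for every pair, so the two branches of section 2.9 give different protection. A preliminary normality test chooses between them. What is at stake is a false claim that one treatment beats another.

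**Working it through.** **The plan's own figure.** The only computed figure is 13 per group for 90% power. It cannot be reproduced, because section 2.6 gives the effect-size formula without means or variances. Solved backwards for two groups, n = 13 implies a standardised difference of about 1.27, which is 1.27/√2 = 0.90 on the plan's err/√(σ₁² + σ₂²) scale. The point below does not depend on it.

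**Inputs.** Four groups, n = 13 each and α = 0.05 (section 2.6); score 0 to 5 (section 2.8.2). Error degrees of freedom: 52 − 4 = 48. Score distributions are assumed, since the article gives none.

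**1. Critical values.** The upper 5% points of the studentised range on 48 degrees of freedom are 2.843 for a span of 2 groups, 3.420 for 3 and 3.764 for 4. For neighbours, 2.843/√2 = 2.011, the ordinary two-sided 5% t value.

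**2. Worst case by formula.** With two equal pairs lying well apart, SNK tests each true null pair at 5%, so the family-wise error is 1 − (1 − 0.05)² = 9.75%. Tukey uses 3.764/√2 = 2.661 for each pair, a two-sided level of 0.0106, and 1 − (1 − 0.0106)² = 2.1%.

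**3. Check on ranks.** Simulation with 6,000 runs per scenario: Kruskal-Wallis at 5% first, then SNK on the joint ranks with the critical values above. The 0 to 5 scores are rounded and truncated normal values.

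| Setting | SNK on ranks | Four-group (Tukey) value on ranks |
|---|---|---|
| All equal, continuous | 4.3% | 4.3% |
| All equal, 0 to 5 scores | 3.7% to 4.1% | same |
| Two equal pairs, continuous, gap 1.27 to 8 SD | 8.9% to 10.0% | 1.9% to 2.1% |
| Two equal pairs, 0 to 5 scores | 9.1% to 10.2% | 1.8% to 2.1% |
| Three equal, one far apart | 9.4% | 6.0% |

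The last row is partly an effect of ranking. The rank variance is (39² − 1)/12 = 126.7 within the three equal groups and (13² − 1)/12 = 14 within the fourth. The pooled value is (3 × 126.7 + 14)/4 = 98.5, which is too small for the three. So putting Tukey critical values on ranks is not a full remedy.

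**4. Dependence on the rank version.** With a fixed standard error taken from all 52 joint ranks, SNK stayed below 5% in every setting run. With a standard error that changes with the number of groups spanned, it gave 6% to 39% for two equal pairs on 0 to 5 scores.

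**5. Which branch.** For rounded scores with an assumed SD of 0.7 to 1.5, Shapiro-Wilk rejected in these proportions:
- one group of 13: 22% to 98%;
- at least one of the four groups: 62% to 100%;
- the 52 pooled values: effectively 100%;
- residuals: 26% to 99%.

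**6. Alternatives.** Across the all-equal and two-pair settings run, Holm-adjusted pairwise rank-sum tests gave 2.0% to 4.8% and Dwass-Steel-Critchlow-Fligner 1.5% to 4.6%. Dunn with Holm gave at most 4.0%, and below 1% with two equal pairs.

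**The case against.** Four replies deserve weight.

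- **About 10% is a worst case.** A reader might infer that the trial would run at twice its nominal error, because the two aPDT arms will be alike and the two others alike. The article does not support that. Its Introduction expects both probiotics and aPDT to work, and section 2.7 lists the scraper for Group 1 only, so nothing shows that Groups 1 and 3 would respond alike. In a graded pattern (control lowest, the two single treatments equal, the combination highest), SNK on ranks gave about 1.5% at a total gap of 0.5 SD, 4% to 5% at 1.6 SD, 6% to 7% at 2 SD and 8% to 9% at 3 SD. This reply stands.
- **The main aim may be untouched.** If only aPDT works, the true null pairs are Group 1 against 3 and Group 2 against 4, so the false claims concern probiotics. That is right for this pattern. If only probiotics work, the null pairs are 1 against 2 and 3 against 4, and the false claims concern aPDT. Neither pattern can be called likely.
- **The branch is not fixed.** A reader might take the nonparametric route as certain because the score is an integer. Step 5 supports likely, no more.
- **No family-wise target is stated, and rank forms of SNK exist.** Both are true. One rank form held the error below 5%, but the text does not select it, and the Tukey branch already applies family-wise control to the same question.

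**Conclusion.** The point holds in limited form. SNK is the named follow-up to Kruskal-Wallis for four groups and does not guarantee a 5% family-wise error. For SNK on ranks with studentised-range critical values, the error is near 4% when all groups are equal and about 9% to 10% when two equal pairs lie apart. These figures assume 13 per group, that rank version and the simulated score shapes; other rank versions gave less than 5% or far more than 10%. The plan is also uneven: the Shapiro-Wilk result decides whether pairwise claims are protected.

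The finding concerns the pairwise comparisons of breath-meter scores between groups only. The global Kruskal-Wallis test and the sample size of 52 are unaffected. It is worth correcting before analysis, but it does not undermine the design.

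**What to change.** In section 2.9, replace SNK with a named rank-based pairwise procedure that controls the family-wise error at 5%: Dwass-Steel-Critchlow-Fligner, or pairwise rank-sum tests with Holm adjustment over the six comparisons. Dunn's test with Holm adjustment is also acceptable but more conservative. State the 5% family-wise level for both branches, so that the protection no longer depends on the normality test.

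This changes one phrase and adds one short statement. No visit, sample or recruitment figure changes. The cost is slightly lower power for each pairwise comparison than with SNK.

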## 3. Discussion

The objective of the present study is to determine whether treatment with aPDT using annatto as the photosensitizer and blue led as the light source is effective at diminishing halitosis in mouth-breathing children. Through this study, we will be able to determine whether there are differences among the proposed treatments. We will also determine whether a reduction in halitosis occurs after the use of photodynamic therapy involving the use of annatto as the photosensitizer and blue LED as the light source and after treatment with probiotics.

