Conventional treatments used in the control of halitosis consist basically of the use of toothpastes and mouthwashes containing bactericidal substances, a tongue scraper, the treatment of dental caries and periodontal disease and the control of xerostomia.^[26]^ Some studies suggest that amine fluoride has a positive effect on diminishing halitosis.^[3]^ Alternative treatments, such as antimicrobial photodynamic therapy (aPDT)^[10,21,27]^ and probiotics, have also been employed in an attempt to control this condition.^[3,16,22,23,26]^ Antimicrobial PDT is treatment in which a photosensitizing agent (dye) produces oxygen free radicals in the presence of light, leading to bacterial cell death. As the main etiological factor of halitosis is the presence of anaerobic bacteria, aPDT (red laser and methylene blue) has demonstrated positive results on the reduction of hydrogen sulfide as well as the bacterial load on the dorsum of the tongue.^[15,21]^ The dye annatto has been evaluated as a photosensitizer in studies on halitosis. This extract from the seeds of the plant Bixa orellana, which is native to Brazil, is accepted by the World Health Organization due to the fact that it is nontoxic.^[1]^ Annatto has antioxidant and antimicrobial properties^[9]^ and recent studies have demonstrated its potential as a therapeutic agent and natural dye.^[28]^

Probiotics are microorganisms that provide health benefits when absorbed by the host and are often used in foods and fermented products as well as pharmaceutical formulations.^[25]^ Studies have shown the positive results of probiotics for the control of halitosis and suggest that these products favor the elimination of undesirable microorganisms and promote the recolonization of the microbiota.^[16,22]^

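### The within-arm paired tests in section 2.9 cannot show that aPDT or probiotics work; conclusions should be tied to the between-group comparison that the plan already contains

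*Protocol article*

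**What the plan says.** Section 2.9 has two layers. The first compares the four groups: ANOVA with Tukey's test, or Kruskal–Wallis with Student–Newman–Keuls. The second compares each arm with itself over time. For parametric data, the t "test will be used for paired data to analyze the results of treatment in the 2 periods of the study". For nonparametric data, the Wilcoxon test "will be used for the comparison of each treatment in the 2 periods of the study". Section 2.7 lists three breath readings (before, immediately after, and 7 days after treatment), and section 2.9 does not say which two are paired.

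The Discussion restates the objective, which is whether aPDT with annatto and blue LED is effective. It first promises an answer on differences among the treatments and then continues: "We will also determine whether a reduction in halitosis occurs after the use of photodynamic therapy". The same sentence extends this to probiotics.

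Three other places bear on the point:
- Section 2.4.1, on entry: children with "halitosis determined using a portable breath meter (score ≥ 2) will be included in the study".
- Section 2.8.2, on the same device: "the odor of the breath is measured and scored on a scale of 0 to 5 points". Section 2.9 analyses this score.
- Section 2.8.8, on care in every arm: "All 52 participants will be instructed to brush with a toothpaste containing amine fluoride", with floss, for 10 days. The Introduction says of this ingredient: "Some studies suggest that amine fluoride has a positive effect on diminishing halitosis".

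**The concern.** A paired test asks whether an arm's mean score moved from its own baseline. It has no comparator, so it credits the arm's label with everything that changed over the period. Here the article itself supplies two other reasons for a fall: a possibly active toothpaste given to every child, and selection of children for a high reading on the outcome device. Either could produce a significant reduction in Groups 2 and 4 with an inert photosensitiser and light, and in Group 3 with an inert probiotic.

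Finding a significant fall in one arm and none in another would not help, because that pattern is not a test of the difference between the arms.

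At stake is the main conclusion. The article offers two routes to the efficacy question, one randomised and one not, and does not say which governs if they disagree.

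**Working it through.** **The plan's own figure.** Section 2.6 gives 13 per group for power 0.90 at two-sided α = 0.05, but prints no means, variances or effect size, so it can be neither confirmed nor refuted. Working backwards with the normal approximation, d = (1.960 + 1.282) × √(2/13) = 1.27 SD, or 1.27/√2 = 0.90 on the article's err/√(σ₁² + σ₂²) scale. The point does not depend on this figure; only n = 13 per arm is carried forward.

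**Check 1: a change shared by all arms.** Let δ be the shared mean change divided by the SD of the within-child differences. With n = 13 the paired t statistic is noncentral t with 12 df and noncentrality δ√13. It is significant when its absolute value exceeds t(0.975; 12) = 2.179. The values of δ are illustrative; the article gives none.

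| Shared change δ | δ√13 | P(paired test significant), no aPDT effect |
|---|---|---|
| 0 | 0 | 5% |
| 0.25 | 0.90 | 13% |
| 0.5 | 1.80 | 38% |
| 0.75 | 2.70 | 70% |
| 1.0 | 3.61 | 91% |

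**Check 2: selection on the outcome device.** This is a simulation of four arms of 13 with no aPDT effect, a score rounded to integers from 0 to 5, entry at 2 or more, and the entry reading used as baseline. Assumed and not in the article: mean in the screened population 1.5, 2.0 or 2.5; SD 1.2; test-retest reliability 0.5, 0.7 or 0.9; and a co-intervention shift common to all arms of 0 or 0.5 points. There were 4,000 simulated trials per scenario for the t test and ANOVA, and 1,000 for Wilcoxon. Entries are the percentage of simulated trials in which one aPDT arm shows a significant reduction. The tests are two-sided at 0.05 and only falls are counted, so the nominal rate is 2.5%.

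| Mean | Reliability | Mean change, selection only | t, selection only | Wilcoxon, selection only | t, plus 0.5-point shift | Wilcoxon, plus 0.5-point shift |
|---|---|---|---|---|---|---|
| 1.5 | 0.5 | −0.52 | 34.3 | 31.6 | 85.1 | 82.9 |
| 1.5 | 0.7 | −0.34 | 21.0 | 17.9 | 84.1 | 81.3 |
| 1.5 | 0.9 | −0.15 | 10.7 | 10.1 | 89.1 | 88.4 |
| 2.0 | 0.5 | −0.37 | 18.0 | 15.0 | 70.2 | 68.2 |
| 2.0 | 0.7 | −0.24 | 12.6 | 11.0 | 71.4 | 68.2 |
| 2.0 | 0.9 | −0.11 | 7.3 | 5.9 | 83.3 | 83.1 |
| 2.5 | 0.5 | −0.24 | 8.9 | 7.6 | 52.9 | 51.9 |
| 2.5 | 0.7 | −0.15 | 7.0 | 7.5 | 58.7 | 56.1 |
| 2.5 | 0.9 | −0.06 | 4.6 | 3.5 | 78.3 | 76.1 |

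In the same runs the four-group ANOVA, on change or on the follow-up score, rejected in 4.4% to 6.1%. Whatever lowers all arms alike cancels in the randomised comparison and does not cancel in the paired one.

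**What is shared, and when.** Ten days of toothpaste bears mainly on the 7-day reading. Regression to the mean, where it operates, affects both post-treatment readings. A further possible shared component is scraping: section 2.8.6 says "Tongue scraping will be performed by the same operator on all participants", while section 2.7 lists a scraper for Group 1 only. Those two sections must be reconciled.

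**The case against.** The strongest reply is that the controlled comparison is already planned and comes first, in section 2.9 and in the Discussion, with the within-arm question introduced as an addition. That stands. A reader might infer that the plan discards its randomisation or has no controlled test of aPDT; the text does not support this, and the simulation shows the between-group test holding its level.

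A reader might also infer that a significant paired test will be declared proof of efficacy, particularly if the ANOVA is null. The Discussion says only that a reduction occurs after treatment, and no passage sets such a fallback. Nor can one say that the ANOVA is likely to be null, since the effect behind the claimed power is not printed. What remains is that the paired tests are described as analysing the results of treatment, sit beside an efficacy objective, and are given no subordinate status.

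Third, regression to the mean is not established. Section 2.4.1 and section 2.7 do not say whether the qualifying reading is also the pre-treatment reading. Section 2.8.2 asks for dietary preparation over the preceding 48 hours, whereas screening starts at a first clinic appointment, so a separate baseline is plausible. With one, this component would largely vanish. The shared toothpaste would remain, though if the two periods are before and immediately after treatment its influence would be small.

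Finally, interpretation rules and covariate adjustment are often left to an SAP, which is not at hand. The point therefore concerns what the article does state: inferential within-arm tests and an aim worded to match them.

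**Conclusion.** The point holds as a should-fix. The within-arm paired tests cannot answer whether aPDT or probiotics are effective, because the article describes influences other than the study treatments that can lower the score in every arm.

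The size is illustrative. Selection alone gives about 5% to 34% significant reductions per arm against a nominal 2.5%, conditional on the entry reading being the baseline and on the assumed mean, SD and reliability. At the favourable end (mean 2.5, reliability 0.9) the excess is small. A shared change of 0.5 to 1.0 SD of the differences gives 38% to 91%; that calculation needs no selection, but the true size of any toothpaste effect is unknown. The randomised between-group comparison is not affected.

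**What to change.** In section 2.9, state that conclusions on aPDT and on probiotics rest on between-group contrasts of the post-treatment breath score adjusted for the baseline score, with confidence intervals. Report within-arm change descriptively, without p-values offered as evidence of efficacy, and name the time points used.

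In the Discussion, reword the second aim as whether the reduction is larger with aPDT, or with probiotics, than without. Reconcile sections 2.7 and 2.8.6 on scraping first, because what a contrast with Group 1 estimates depends on who is scraped.

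The cost is a few sentences; the baseline score is already collected. Stating whether the qualifying reading is also the baseline would help. A separate baseline reading is an optional extra and is not needed for the fix.
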